### 2.2. Participants

Patients are eligible for inclusion if they fulfill the following criteria: patients with chronic kidney disease (CKD) on stage G3b to G5 who have not yet started HD, aged from 18 to 75 years old, who are planned for a first native AVF surgical creation as decided by a multidisciplinary team comprising nephrologists and vascular surgeons, irrespective of previous aPL status.

Exclusion criteria are the following: ESKD patients switching from peritoneal dialysis to HD, AVF creation not feasible surgically or technically, endovascular AVF, innate or acquired thrombophilia other than APS, active neoplasia, aPL assays not relevant (because of anti-vitamin K treatment, inflammatory state, absence of confirmation assay, etc.).

### 2.3. Study Groups

We classified patients according to the new APS 2023 ACR/EULAR classification criteria. Patients are undergoing a clinical and laboratory assessment, allowing for the evaluation of criteria clustered into six clinical domains (macrovascular venous thromboembolism, macrovascular arterial thrombosis, microvascular, obstetric, cardiac valve, and hematologic) and two laboratory domains [7]. The patients are divided into the following two groups:

aPL positive arm: gathering all patients with aPL persistent positivity (laboratory domains), including:

APS: patients with at least three points in both clinical and laboratory criteria according to the 2023 ACR/EULAR classification criteria for APS.

aPL carriers without APS: patients with at least three points in laboratory criteria but fewer than three points in clinical criteria

aPL negative arm: gathering patients with one (or more) negative aPL assay(s), or patients with an initial positive assay but showing a negative control assay at the 12-week follow up.

Given the heterogeneity of the aPL positive arm, the two subgroups (APS and aPL carriers) will be analyzed to explore AVF maturation failure, thrombosis, stenosis and patency.

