## 1. Introduction

End-stage kidney disease (ESKD) is characterized by the need to initiate renal replacement therapy to control clinical, biological, and hemodynamic complications. Renal transplantation, peritoneal dialysis, and hemodialysis (HD) are currently the treatment options for ESKD. The Kidney Disease Outcomes Quality Initiative (KDOQI) guidelines advocate for the use of native arteriovenous fistula (AVF) as the primary option for establishing HD vascular access in patients with ESKD [1]. Arteriovenous fistula is associated with lower morbidity and mortality compared to arteriovenous grafts or the placement of a HD central venous catheter [2].

AVF creation consists of performing a surgical or endovascular anastomosis of a native artery to an adjacent native vein of the non-dominant superior limb. AVF creation encompasses the outflow vein structural changes characterized by an increased efferent vein diameter, thickness and blood flow [3,4]. This process, usually called “maturation”, takes place within 6 weeks to 3 months and is crucial for routine AVF puncture in HD [5]. Maturation failure of a native AVF is a frequent complication and is characterized by the absence of, or a delay of, maturation, defined either clinically or by using Doppler ultrasound (US) [3,6].

Antiphospholipid syndrome (APS) is an autoimmune disease characterized by the persistent positivity of at least one antiphospholipid antibody (aPL). It is an acquired thrombophilia that affects both the arterial and the venous vasculature. New classification criteria were released in 2023, based on a scoring system [7]. With respect to laboratory domains, the following antibodies are included: lupus anticoagulant (LA); the IgG or IgM anti-cardiolipin antibody (aCL); and the IgG or IgM anti β2 glycoprotein I (aβ2-GPI). Confirmation of a positive assay is mandatory at 12 weeks, leading to confirming the biological criterion. In the absence of any clinical criteria, aPL persistent positivity does not allow for the diagnosis of APS. It is interesting to note that the 2023 ACR/EULAR classification criteria no longer consider isolated positivity of IgM aCL and/or IgM aβ2-GPI [either at moderate titers (40–79 units/mL) or high titers (>80 units/mL)] as sufficient in order to classify a patient as having APS [7].

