### 2.5. Data Collection

In order to limit aPL false positivity, we aim to evaluate aPL profile before AVF creation and HD initiation. Antiphospholipid antibody assays are collected at the time of registration in the study. If not performed, the 12-week follow-up confirmation assay is performed at the time of registration, and before AVF creation.

Lupus anticoagulant (LA) positivity is assessed by using a three-step diagnostic procedure: screening, mix and confirmation procedures using diluted Russell’s viper venom (dRVVT-Siemens^®^, Muenchen Germany) and Silica Clotting time (SCT-Werfen^®^, Barcelona, Spain). Results are expressed as screening-to-confirmation ratios. LA is confirmed if one of the two functional coagulation assays (dRVVT or SCT) is positive in terms of screening-to-confirmation ratio, using a citrated plasma sample (3.2%). The determination of IgG/IgM aCL and IgG/IgM aβ2GPI is performed by a chemiluminescence immunoassay (HemosIL Acustar aCL IgM/IgG Kit and aβ2GPI IgM/IgG kit- Werfen^®^). According to the standards of our laboratory, the results are interpreted as positive (>the 99th percentile) or negative when the IgG or IgM titers were, respectively, >20 U/mL or ≤20 U/mL. Baseline characteristics will be collected at the time of AVF surgical creation and are presented in Table 1.

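### The protocol does not determine the study arm of some persistently aPL-positive patients, because the arm header, the three-point subgroups and the laboratory cut-off disagree

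*Protocol article*

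**What the plan says.** Three parts of the protocol article bear on who counts as exposed.

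- **Section 2.3, positive arm.** The header is inclusive: "gathering all patients with aPL persistent positivity (laboratory domains), including". Two subgroups follow. APS is "patients with at least three points in both clinical and laboratory criteria according to the 2023 ACR/EULAR classification criteria for APS". Carriers without APS are "patients with at least three points in laboratory criteria but fewer than three points in clinical criteria". The section then treats these as the make-up of the arm: "the two subgroups (APS and aPL carriers) will be analyzed".
- **Section 2.3, negative arm.** It is described as "gathering patients with one (or more) negative aPL assay(s), or patients with an initial positive assay but showing a negative control assay" at 12 weeks.
- **Section 2.5, laboratory rule.** For aCL and aβ2GPI, "the results are interpreted as positive (>the 99th percentile) or negative when the IgG or IgM titers were, respectively, >20 U/mL or ≤20 U/mL".
- **Introduction, 2023 criteria.** These criteria "no longer consider isolated positivity of IgM aCL and/or IgM aβ2-GPI" as sufficient to classify APS, whether at moderate (40–79 units/mL) or high (above 80) titre.

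**The concern.** aPL status is the exposure in the primary comparison, so every enrolled patient needs exactly one arm. The positive arm has two thresholds: persistent positivity (the header, read with the 20 U/mL cut-off) and at least three laboratory points (both subgroups). A patient can meet the first and miss the second. The negative arm does not clearly take that patient either, and its wording has an ambiguity of its own. Whoever builds the analysis set must then choose, and the choices give different arm sizes and different estimated failure rates.

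**Working it through.** **Step 1: does isolated IgM reach three laboratory points?** Section 2.3 makes APS equal to at least three clinical and at least three laboratory points. Suppose persistent isolated IgM supplied three laboratory points. A patient with that profile and three clinical points would then be classified as APS. The Introduction says isolated IgM is not sufficient for this, even at high titre. So isolated IgM scores under three. Below 40 U/mL this holds provided a lower titre does not score more than a higher one.

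**Step 2: run each profile through the rules.**

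| Confirmed profile | Header + cut-off | Three-point subgroup | Unconfirmed at 12 weeks |
|---|---|---|---|
| At least three laboratory points | positive | APS or carrier | no |
| Positive, then negative at 12 weeks | not persistent | none | yes, so negative arm |
| Isolated IgM >20 U/mL on both rounds | positive | **none** | no |
| IgG above 20 but below 40 U/mL on both rounds | positive | not stated; none if that band scores under three | no |

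The third row follows from the text. The fourth is conditional, because the document gives no points by titre band.

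**Step 3: the negative-arm wording.** The panel in Section 2.5 is LA, aCL IgG/IgM and aβ2GPI IgG/IgM. If *assay* means a test in that panel, a patient with persistent LA and a negative aCL has one negative assay and meets the negative-arm wording while also being persistently positive. If it means a testing round, that overlap goes away, but the isolated-IgM patient, positive at both rounds, is not negative. Section 2.3 does not say which is meant.

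**Step 4: illustration of the stakes.** The plan states no arm sizes, so there is no figure of its own to reproduce here. From the plan: failure rates of 50% and 70%, two-sided alpha of 0.05 and 100 patients (Section 2.1). Assumed: 35 positive by the cut-off (the Introduction says prevalence in HD patients can exceed 35%), of whom 20 score three points and 15 do not, and 65 negatives.

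Power = Φ[(d − 1.96·SE0)/SE1], where d is the difference in rates, SE0 = √[p̄(1−p̄)(1/n1+1/n2)] with p̄ the pooled rate, and SE1 = √[p1(1−p1)/n1 + p2(1−p2)/n2].

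Worked once for 35 vs 65 at 70%/50%: p̄ = (24.5+32.5)/100 = 0.57; SE0 = 0.1038; SE1 = 0.0992; (0.20 − 1.96×0.1038)/0.0992 = −0.035; power 0.486.

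| Gap patients' true risk | Handling | Comparison | Power |
|---|---|---|---|
| 70% | counted positive | 35 vs 65, 70% vs 50% | 49% |
| 70% | dropped | 20 vs 65, 70% vs 50% | 34% |
| 70% | counted negative | 20 vs 80, 70% vs 53.75% | 25% |
| 50% | counted negative | 20 vs 80, 70% vs 50% | 35% |
| 50% | counted positive | 35 vs 65, 61.4% vs 50% | 19% |

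The mixed rates are (65×0.50 + 15×0.70)/80 = 0.5375 and (20×0.70 + 15×0.50)/35 = 0.614.

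With 5 to 20 patients in the gap, taken from the same 35, power runs from 44% to 27% when they are dropped, from 40% to 18% when they are counted negative at 70% risk, and from 37% to 13% when they are counted positive at 50% risk.

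**The case against.** The best defence is that the header settles the arm. It covers all persistent positives and ends with *including*, which need not introduce a complete list. Section 2.8 uses the same split, with and without persistent positivity, and the subgroups serve exploration only. On that reading an isolated-IgM patient is positive without a subgroup. This is a fair reading, and it rules out the stronger claim a reader might make, that these patients belong to neither arm. The text does not establish that. It leaves the arm undetermined, because the same section treats the two subgroups as making up the arm and says patients were classified by the 2023 criteria.

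The objection stands on four further points.

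- Read with the sentence that follows, the negative-arm phrase most naturally counts testing rounds. The overlap with the positive arm exists only on the literal reading.
- A reader might infer that a patient with IgG at, say, 25 U/mL certainly falls in the gap. The documents give 40–79 and above 80 only in a remark about isolated IgM and give no point values, so this stays conditional.
- A reader might set every scenario against 49% power. That comparator holds only if gap patients carry 70% risk. If they carry 50%, the comparator is 35% (20 vs 80).
- The documents do not show that allocation will be decided with outcomes in view. Assays are done before AVF creation, and the full protocol and SAP are not at hand.

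The conflict itself remains. It lies between rules the article states, not in detail it left out.

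**Conclusion.** Wrong as written. The exposure rule for the primary comparison is not internally consistent, and the arm of some patients is not determined. This is firm for persistent isolated IgM, conditional for IgG between 20 and 40 U/mL, and a matter of ambiguous wording for the negative arm. The number of patients affected is unknown, and the 20/15/65 split is assumed. Under that split, the handling of 15 patients moves power between 25% and 49% if they share the exposed risk, and between 19% and 35% if they share the control risk. Which handling does better depends on a risk that is not known in advance, so the figures do not show that either definition is the right one. They show that the choice matters and should be fixed in advance.

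**What to change.** Before any outcome is analysed:

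1. Reconcile the header, the three-point subgroups and the laboratory cut-off into one exhaustive and mutually exclusive rule, and state whether the primary exposure is persistent positivity by the cut-off or at least three laboratory points.
2. Define the negative arm as all assays in the panel negative, or an initial positive not confirmed at 12 weeks.
3. Report persistent positives with fewer than three laboratory points as their own subgroup, next to APS and carriers.
4. Run whichever definition is not primary as a pre-specified sensitivity analysis.

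The cost is a change of wording and one extra analysis, using assay results the study already collects. Each choice has a price: a cut-off definition dilutes the contrast if low-level aPL carry no risk, and a three-point definition leaves fewer exposed patients. The sensitivity analysis would show how far the result depends on that choice.

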### 2.4. Follow Up

Participants will be followed clinically for 1 year after the date of AVF creation (Figure 1. Study protocol).

### 2.5. Data Collection

In order to limit aPL false positivity, we aim to evaluate aPL profile before AVF creation and HD initiation. Antiphospholipid antibody assays are collected at the time of registration in the study. If not performed, the 12-week follow-up confirmation assay is performed at the time of registration, and before AVF creation.

Lupus anticoagulant (LA) positivity is assessed by using a three-step diagnostic procedure: screening, mix and confirmation procedures using diluted Russell’s viper venom (dRVVT-Siemens^®^, Muenchen Germany) and Silica Clotting time (SCT-Werfen^®^, Barcelona, Spain). Results are expressed as screening-to-confirmation ratios. LA is confirmed if one of the two functional coagulation assays (dRVVT or SCT) is positive in terms of screening-to-confirmation ratio, using a citrated plasma sample (3.2%). The determination of IgG/IgM aCL and IgG/IgM aβ2GPI is performed by a chemiluminescence immunoassay (HemosIL Acustar aCL IgM/IgG Kit and aβ2GPI IgM/IgG kit- Werfen^®^). According to the standards of our laboratory, the results are interpreted as positive (>the 99th percentile) or negative when the IgG or IgM titers were, respectively, >20 U/mL or ≤20 U/mL. Baseline characteristics will be collected at the time of AVF surgical creation and are presented in Table 1.

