Although ESKD is rare in APS, the prevalence of persistent aPL positivity is higher in HD patients compared to the general population, and can reach more than 35% [8]. The reason for such a high prevalence of aPL positivity in HD is not well known. Several hypotheses have been proposed such as (a) molecular mimicry as a response to the exposure to microorganisms, endotoxins or HD membranes, or (b) a response to oxidation (i.e., cross-reactive immunoglobulins against epitopes of oxidized lipids) [8]. Nevertheless, aPL positivity has been inconsistently associated with AVF thrombosis [8,9,10,11]. Also, aPL positivity has been rarely associated with AVF stenosis [12] and intrastent restenosis [13]. Recently, our group published the first report of a significant association between aPL persistent positivity, and native AVF maturation failure as defined by US in a retrospective study including 116 HD patients [14]. The aPL positivity was a strong predictor of AVF maturation failure in multivariate analysis.

The aim of the present study is to confirm this association in a prospective cohort. The primary outcome of the study is to examine the possibly causative link between aPL persistent positivity and the occurrence of AVF maturation failure defined by the clinical approach combined with US.

Secondary outcomes will focus on clinical outcomes other than AVF maturation: functional primary patency and primary patency, time to AVF complications, AVF thrombosis or stenosis rates, bleeding complications rates and HD adequacy parameters.

In addition, in order to better understand the underlying pathophysiological mechanism of AVF maturation failure in aPL positive patients, we will perform blood analyses as well as an in vitro study using cultured immortalized human microvascular endothelial cells type 1 (HMEC-1).

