### 2.8. Statistical Analyses

The total expected sample size is assumed to be a minimum of 100 patients based on an average recruitment rate of 2 patients/month. Analyses will describe AVF clinical outcomes for patients with and without persistent aPL positivity, potential predictors of patient outcome. Analyses will use all available data, regardless of final sample size.

Data will be expressed as mean ± standard deviation (SD) for variables with a normal distribution or as median ± interquartile range (P25; P75). Student’s t-test will be used to compare the means of the quantitative variables following a normal distribution by group. The Mann–Whitney Wilcoxon test will be used to study the variation between two groups of variables following an asymmetric distribution. The significance level of the tests was 0.05 with odds ratios and 95% confidence intervals. Multivariate models will be performed through logistic regression for variables showing statistically significant differences between groups.

We will employ Kaplan–Meier survival analysis to estimate the probability of AVF primary patency and functional primary patency over time.

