**Figure 2 life-15-00168-f002:**
[figure not shown]
Pathophysiological hypothesis of aPL-associated AVF maturation failure. The first line represents the pathways implicated in the pathophysiology of APS and the second line represents the presentation of AVF maturation failure (either in the presence of thrombosis, stenosis or because of insufficient venous remodeling). The dashed arrows represent pathophysiological hypotheses that have not been studied in the literature, while the solid arrows represent associations described in the literature. MCP-1: Monocyte Chemotactic Protein 1, MMP: matrix metalloproteases, mTOR: mammalian Target of Rapamycin, NO: nitric oxide, TIMP-1: tissue inhibitor of metallo-proteinase-1.

**Table 1 life-15-00168-t001:** Baseline characteristics collected at the time of AVF surgical creation.

Parameters	
Demographics	Age
	Gender
	BMI (kg/m^2^)
	Ethnicity
	Smoking status
Treatments	Anti-platelet therapy
	ACE/ARBs
	Statins
	Erythropoietin
	Anticoagulation therapy
	Beta-blockers
Medical history	Etiology of CKD, histologically proven
	Diabetes mellitus
	Hypertension
	Coronary heart disease
	Stroke or TIA
	Ischemic heart disease
	Peripheral vascular disease
	Left ventricular ejection fraction
	Deep vein thrombosis (n, %)
	Other aPL related clinical features
Biological	Hemoglobin level
features	Platelet count, mean platelet volume
	Coagulation tests: activated PTT, fibrinogen, Prothrombine time
	Lipids
	c-reactive protein, ESR
	Nt-proBNP
Vascular access	Need for catheter before AVF use
parameters	AVF creation date, AVF type, surgical procedure information (type of anesthesia, artery and vein diameter, anastomosis diameter)
	Mapping details
	Perioperative complications: bleeding, local hematoma, other complications
	Pre-operative Flow mediated dilation of the brachial artery as a marker of endothelial dysfunction

ACE: angiotensin-converting enzyme inhibitors; ARB: angiotensin II receptor blockers; AVF: arteriovenous fistula; BMI: body mass index; CRP: c-reactive protein; TIA: transient ischemic attack.

**Table 2 life-15-00168-t002:** Primary and secondary outcomes.

Primary Outcomes	
AVF maturation	Defined 6 weeks after AVF creation, by US: AVF brachial artery blood flow > 600 mL/min, outflow vein diameter > 6 mm;

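### Table 1 lists no measure of kidney function in a cohort spanning CKD G3b to G5, so adjustment of the aPL odds ratio for it is not assured

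*Protocol article*

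**What the plan says.** - **Baseline list.** Section 2.5 sends the reader to one place for baseline data: "Baseline characteristics will be collected at the time of AVF surgical creation and are presented in Table 1".
- **What Table 1 holds.** It goes down to mean platelet volume, ESR, NT-proBNP, type of anesthesia, anastomosis diameter and flow-mediated dilation. Its only kidney item is "Etiology of CKD, histologically proven". It has no row for eGFR, creatinine, urea or CKD stage. The Kt/V and urea reduction ratio in Table 2 are on-dialysis outcome measures, not baseline kidney function.
- **Range of the cohort.** Section 2.2 admits "patients with chronic kidney disease (CKD) on stage G3b to G5 who have not yet started HD".
- **Adjustment rule.** Section 2.8: "Multivariate models will be performed through logistic regression for variables showing statistically significant differences between groups".
- **aPL and kidney disease.** The Introduction says that "the prevalence of persistent aPL positivity is higher in HD patients compared to the general population, and can reach more than 35" per cent. It calls the reason poorly understood and offers two hypotheses: "molecular mimicry as a response to the exposure to microorganisms, endotoxins or HD membranes", and "a response to oxidation".
- **Outcomes.** Table 2 defines maturation by ultrasound at 6 weeks, and clinically by sustained two-needle use in dialysis sessions. Time to first puncture is also listed among the primary outcomes. Clinical follow-up is one year (Section 2.4).

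**The concern.** The study compares two groups that are not randomized, and its stated aim is to examine a possibly causal link between persistent aPL positivity and maturation failure. A baseline factor related to both would bias the aPL odds ratio unless it is adjusted for. Kidney function is a reasonable candidate, because the cohort covers a wide range of it.

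Two things are at stake.

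1. **Confounding.** If aPL-positive patients have more advanced CKD, and advanced CKD goes with poorer maturation, part of an observed aPL association would belong to kidney function.
2. **Opportunity to observe the outcome.** No patient is on HD at entry. Clinical maturation and puncture for dialysis can be seen only after HD starts, and baseline kidney function plausibly influences when that happens within the one-year follow-up. If it is not a listed variable, the report cannot readily show that the two aPL groups had a similar chance of reaching HD. This second link follows from the outcome definitions and needs no effect of kidney function on the vein.

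**Working it through.** **Step 1. The text.** Reading every row of Table 1 against Section 2.2 gives 0 rows for kidney function and 1 row for the cause of CKD. Section 2.8 selects covariates by significant difference between groups; the groups defined in Section 2.3 are aPL positive and aPL negative. So kidney function is not a listed candidate. Even if it were listed, it would enter only if it passed the screen.

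**Step 2. The plan's own effect size.** Section 2.1 plans for 70% versus 50% failure: 20 points, odds ratio (0.70/0.30)/(0.50/0.50) = 2.33.

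**Step 3. Possible size of confounding, no true aPL effect.** All inputs are assumptions; the article gives none. Let q be the share of an aPL group at stage G5, and f5 and f4 the failure rates in G5 and in G3b–G4. Failure in a group is F = q·f5 + (1 − q)·f4.

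| q, aPL+ vs aPL− | f5, f4 | F, aPL+ | F, aPL− | Difference | Odds ratio |
|---|---|---|---|---|---|
| 0.60 vs 0.50 | 0.60, 0.50 | 0.36 + 0.20 = 0.56 | 0.30 + 0.25 = 0.55 | 0.01 | (0.56/0.44)/(0.55/0.45) = 1.04 |
| 0.70 vs 0.50 | 0.70, 0.40 | 0.49 + 0.12 = 0.61 | 0.35 + 0.20 = 0.55 | 0.06 | (0.61/0.39)/(0.55/0.45) = 1.28 |
| 0.80 vs 0.50 | 0.70, 0.40 | 0.56 + 0.08 = 0.64 | 0.35 + 0.20 = 0.55 | 0.09 | (0.64/0.36)/(0.55/0.45) = 1.45 |

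**Step 4. A second parametrization.** Assume half the cohort is at an advanced stage, 35% are aPL positive, failure is 50% in aPL negatives, and advanced stage has the same odds ratio with aPL as with failure. The spurious aPL odds ratio is then 1.04 (both 1.5), 1.12 (both 2) or 1.33 (both 3). For the last case:

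- aPL prevalence is 0.471 in advanced and 0.229 in less advanced stages (mean 0.35).
- The advanced share is 0.5 × 0.471/0.35 = 0.673 in aPL positives and 0.5 × 0.529/0.65 = 0.407 in aPL negatives.
- Failure rates of 0.659 (advanced) and 0.391 (less advanced) give 50% in aPL negatives.
- Failure in aPL positives is 0.673 × 0.659 + 0.327 × 0.391 = 0.571, so the odds ratio is 0.571/0.429 = 1.33.

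If either link is set to 1, the spurious odds ratio is 1.00.

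**Step 5. Would the significance screen admit stage if it were listed?** Take the middle row of Step 3 (G5 share 70% vs 50%) with an assumed 35 aPL-positive and 65 aPL-negative patients. The pooled share is 0.57. The standard error is √(0.57 × 0.43 × (1/65 + 1/35)) = 0.104 under the null and √(0.25/65 + 0.21/35) = 0.099 under the alternative. The chance of p < 0.05 is Φ((0.20 − 1.96 × 0.104)/0.099), about 49%. An imbalance large enough to give a spurious odds ratio of 1.28 would be left out of the model about half the time.

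**The case against.** **Kidney function is not lost.** CKD stage must be established for each patient to apply the inclusion criterion, and plasma and serum taken before fistula creation are stored (Section 2.6). Section 2.8 does not say that candidates come only from Table 1. A reader might infer that kidney function can never enter the model; the documents do not support that. This stands. It makes the fix cheap, but it does not put the variable on the list or in the model.

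**This is a journal article.** The full protocol or case report form may carry the field. That is fair, and it limits the weight of the point. However, the article names Table 1 as the baseline list, the table is detailed, and the screening rule in Section 2.8 would apply in any case.

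**Confounding is not shown.** A reader might infer from the Introduction that kidney failure is an established common cause of aPL positivity and of failed maturation. It is not established there. The comparison is HD patients against the general population, not across G3b to G5. One proposed mechanism, exposure to dialysis membranes, cannot act before HD, and aPL is measured before HD to limit false positives. Oxidation might track kidney function, but the article does not say so. Nothing in it links stage to the 6-week ultrasound result. This stands, so the confounding is plausible and not documented.

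**Adjustment is the wrong tool for unobserved outcomes.** This also stands. Entering eGFR does not supply a clinical maturation result for a patient who has not started HD.

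**Conclusion.** The point holds as a gap in the planned data list and adjustment. Kidney function is absent from the stated baseline list in a cohort that spans G3b to G5, and the covariate rule does not secure adjustment for it. It is a plausible confounder of the association between aPL and maturation, and a plausible influence on whether and when the HD-dependent outcomes can be seen.

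The possible bias rests wholly on assumed stage shares, failure rates and direction. Across the cases shown it is 1 to 9 percentage points, odds ratio 1.04 to 1.45, against the planned 20 points and 2.33. It is nil if kidney function is unrelated to aPL or to failure. A reader might infer that confounding by stage could produce the whole planned effect; these figures do not support that. It could distort a more modest estimate, which matters for a study with a causal aim. The change is worth making because it is nearly free; the omission does not invalidate the design.

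**What to change.** 1. Add eGFR and CKD stage at fistula creation to Table 1, taken from routine laboratory results. Stage at screening may differ, given the 12-week aPL confirmation interval.
2. Name eGFR as a prespecified covariate in the adjusted aPL model for the maturation outcomes, whether or not it differs significantly between groups. Listing it without this step leaves it subject to the screen in Section 2.8.
3. Report aPL prevalence by CKD stage, so that readers can see whether the link to exposure exists in this cohort.

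If the case report form already captures eGFR, only the Table 1 entry, the model statement and the tabulation are needed.

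**Cost.** One data field, no new test, and one model term in about 100 patients. With an assumed 65 aPL-negative and 35 aPL-positive patients at the planned rates, there would be 32.5 + 24.5 = 57 failures and 43 non-failures. One continuous term is affordable, though it uses some of the room for other covariates.

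**Limit.** This does not settle how to handle clinical maturation and first puncture in patients who have not started HD. That needs its own rule; recorded eGFR would only help to describe those patients by aPL group.
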